## Abstract

**Background:**

An increasingly vocal movement of patients with systemic complaints, supposedly linked to polypropylene mesh implants, is leading to increasing numbers of patient-preferred mesh-less surgical repairs for inguinal hernia, stress urinary incontinence, and pelvic organ prolapse. However, current literature does not support any association between polypropylene implants and Autoimmune Syndrome Induced by Adjuvants (ASIA). This prospective pilot aims to examine autoimmunity in patients in whom ASIA is suspected, based on previously described criteria. We aim to demonstrate the effectiveness of mesh allergy testing and to investigate the natural evolvement of ASIA symptoms or the effect of mesh removal on ASIA complaints.

**Methods:**

This multi-centre, prospective pilot study will include patients with symptoms of the ASIA syndrome according to Shoenfeld’s Criteria. Physical examination, immunologic blood tests, and mesh allergy tests will be performed by an experienced immunologist and surgeon. Questionnaires on improvement of symptoms, psychological susceptibility, and connective tissue disease will be collected at predefined time points. When patients’ wish for mesh removal is persistent, mesh implants will be removed surgically. All meshes will be assessed histopathologically. Follow-up is 12 months.

**Discussion:**

Current evidence on a causal relation between polypropylene mesh and ASIA syndrome is lacking. In this study, mesh allergy testing will be evaluated as a potential first objective screening test for inflammation-like response specific to polypropylene, in patients meeting diagnostic criteria for ASIA syndrome following polypropylene implantation. This study will be performed to add to existing literature on ASIA with polypropylene adjuvants and to help reduce knowledge gaps on diagnosis and prognosis.

## Introduction

Inguinal hernia repair is one of the most frequently performed surgeries in the Netherlands (27,000 to 30,000 yearly), with a vast variety in possible approaches. Whereas initial surgical procedures had significant risk of recurrence, the introduction of polypropylene (PP) meshes reduced the incidence of recurrence drastically [1–3]. Nowadays, a mesh-based repair is the preferential treatment, either endoscopically or via an ‘open’ approach [4, 5]. Subsequently, synthetic mesh has found its way into other pelvic reconstructive surgery. Stress Urinary Incontinence (SUI) and Pelvic Organ Prolapse (POP) have been treated with PP mid urethral slings and mesh implants respectively, since the ‘90s. The rationale for the use of PP-implants is similar; the high recurrence rate (14%–17%) after autologous repair declined significantly after introduction of the use of mesh [4, 6, 7].

As recurrence risk has greatly declined in abdominal wall and urogynaecological surgery, research attention has shifted towards other complications. Approximately 0.5%–6% of patients operated for inguinal hernia develop chronic postoperative inguinal pain (CPIP) that severely influences daily life and limits work performance [4]. In POP or SUI repair, mesh erosion and mesh exposure can lead to extensive morbidity, ultimately discouraging the use of mesh implants in these procedures [7, 8]. Apart from CPIP, and mesh erosion/exposure in vaginal PP mesh implantation, patients seldomly report subjective systemic complaints after polypropylene mesh implantation, such as chronic fatigue, pyrexia, and myalgia [9, 10].

However, in the last three odd years these non-specific, potentially mesh-related, complaints after pelvic and inguinal hernia repair have gained awareness in the (inter)national scientific society whereas several media have highlighted these refractory postoperative complications. In research and lawsuits, patients’ concerns are rapidly increasing in suit. Due to earlier safety problems with transvaginal meshes and growing concerns of the possibility of a chronic foreign body reaction to the mesh, patients now unconditionally oppose polypropylene mesh implants [11]. Concurrently, hernia mesh lawsuits are becoming more prevalent in the United States as well as in the Netherlands [12–14].

Local morbidity associated with the implantation of mesh in urogynaecological surgery has led to a more negative connotation of mesh in these fields. While not directly attributable to its increasing popularity, widespread media coverage on the negative effects of implants in recent decades, such as breast implant illness, seems to correlate strongly with the increased interest of patients and their advocates in polypropylene-related illness [15–18]. For instance, some patients report inflammation-like symptoms following polypropylene mesh implantation, suggesting the presence of a systemic autoimmune response or a so called “Autoimmune/autoinflammatory Syndrome Induced by Adjuvants” (ASIA syndrome, formerly known as Shoenfeld’s syndrome) [19, 20]. These symptoms include myalgia, arthralgia, chronic fatigue, fever, swelling and other non-specific and subjective symptoms.

Despite differences in composition of these implants, their placement in the human body and the proposed mechanism(s) of induction of illness (such as silicone migration or encapsulation), form the rationale for the grouping of all implants and implant-related complications to an autoimmune disorder or syndrome [21]. Concerns regarding these effects of various implants occupy the minds of both professionals and patients [16, 21]. Subsequently, data on true incidence of autoimmune diseases after polypropylene implantation are currently unavailable. However, estimations are up to 3%, which is equal to its incidence in the general population [6, 22].

So far, solid evidence of a causal relation between mesh implantation and systemic autoimmune or autoinflammatory response is lacking. In 2021, a systematic review and meta-analysis was performed considering all available evidence on the association between PP implants for pelvic floor surgery and inguinal hernia repair and autoimmune/autoinflammatory diseases [23]. It was concluded that: *“to date, there is no evidence to suggest a causal relationship between implantation of PP mesh and the occurrence of autoimmune disease”* [23].

In the present pilot study, a possible relation between the implantation of PP mesh for inguinal hernia repair, SUI or POP and subsequent systemic autoimmune complaints will be investigated by testing immunologic and allergic responses before and, on indication, after mesh removal. Additional value of Mesh Allergy Testing (MAT) shall be assessed as a measure to objectify these complaints. If so, a profound insight in diagnostics for systematic complaints will be attained that may provide new directions for future treatment.

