### Participants

Fifty consecutive patients with suspected systemic autoimmune/autoinflammatory response or ASIA syndrome will be recruited from one of the five aforementioned departments. In the present study, patients are considered to have ASIA when at least three major criteria from Table 1 are present, as previously published [17]. Only referrals from the outpatient ASIA clinics will be accepted and no active recruitment will be undertaken. Subjects will be eligible for inclusion if they meet all of the following criteria:- Patients >18 years of age and written informed consent obtained;- Suspected ASIA syndrome after elective inguinal hernia, POP, or SUI repair, defined as at least three major ASIA criteria (Table 1), of which the exposure to an external stimulus (PP mesh) is one;- ASIA complaints started specifically after the implantation of PP mesh and were not present before the surgical repair.

**TABLE 1 T1:** Diagnostic criteria autoimmune/autoinflammatory syndrome induced by adjuvants (ASIA) syndrome [17].

Major criteria
- Removal of inciting agent induces improvement
- Exposure to an external stimulus (infection, vaccine, silicone, adjuvant) prior to clinical manifestations
- The appearance of ‘typical’ clinical manifestations:
- Myalgia, myositis or muscle weakness
- Arthralgia and/or arthritis
- Chronic fatigue, unrefreshing sleep or sleep disturbances
- Neurological manifestations (especially associated with demyelination)
- Cognitive impairment, memory loss
- Pyrexia
- Sicca (dry mouth and/or dry eyes)
- Typical biopsy of involved organs
Minor criteria
- The appearance of autoantibodies or antibodies directed at the suspected adjuvant
- Other clinical manifestations (e.g., irritable bowel syndrome)
- Specific HLA (e.g., HLA DRB1, HLA DQB1)
- Evolvement of an autoimmune disease (e.g., multiple sclerosis, systemic sclerosis)

Patients will be excluded from participation in this study if one or more of the following is present:- Known autoimmune/inflammatory disorders;- Known malignancies;- (Low grade) infections or other inflammatory diseases at time of surgery;- Cognitively impaired individuals.- Recent (<3 months) vaccination

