### Outcomes

Primary outcome is the value of MAT as an objective diagnostic test for patients who fit the current ASIA criteria. Secondary outcomes include the value of immunologic blood tests, and the association between both subjective outcomes (autoimmune/autoinflammatory symptoms) and objective findings (MAT, blood test).

Another secondary outcome is the success rate of (partial) mesh removal for the resolution of subjective complaints. This success rate is defined as a complete resolution of subjective complaints (on CSQ) and ASIA symptoms (Table 1) and the report of a “much better” or “very much better” condition on PGI-I.

Baseline and dynamic patient demographics will be collected, including age, gender, ASA classification (American Society of Anaesthesiologists), year of PP implantation and type of PP implant, duration of ASIA complaints, pain scores (using Numerical Rating Scale; NRS), body mass index (BMI) smoking status, medication use (including immunosuppressants), previous imaging, time of resolution of symptoms, and remaining symptoms.

Additionally, in case of surgical mesh removal, the following parameters will be collected: intraoperative macroscopic configuration of mesh, duration of surgery, additionally performed neurectomy, and complications. All explanted meshes will be examined histopathologically to check for granulomatous inflammatory or acute inflammatory reactions surrounding the explant.

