### Statistical Methods

Baseline patient demographics will be presented as descriptive statistics. Primary outcome (rate of positive diagnostic tests) will be presented as descriptive statistics (percentage of positive tests) at all predefined time points.

Secondary outcomes include the association between subjective (questionnaire outcomes evaluating systemic symptoms or ASIA symptoms) and objective findings (MAT, blood test). For this outcome, subjective complaints are summed (each complaint is 1 point). Objective findings are dichotomized. The association between the number of subjective complaints and the presence of objective findings is subsequently calculated via Chi-Square Test or Fisher’s Exact Test in low expected counts, where applicable. For missing data, percentage of data present will be described. If known, a rationale for missing data will be presented. If only limited data is missing per variable, analysis will proceed as expected. Imputation of missing data is not preferred as imputation within the relatively small sample size would decrease validity of the study, as well as the intention to present real data as it is.

A p-value <0.05 is considered statistically significant. Success rates of (partial) mesh removal will be presented as descriptive statistics (percentage of successful surgery).

Patients are considered to have ASIA when either two major or one major and two minor criteria are present (adapted from Cohen Tervaert 2018) [17]. In the present study, we only considered patients to have ASIA when at least three major criteria are present.

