This pilot aims to assess the diagnostic value of Mesh Allergy Testing as a first objective screening tool, to aid physicians in decision-making for possible treatments (including high-risk mesh removal) [26, 27]. MAT has not been validated as a test for screening systemic reaction to an adjuvant before, necessitating the current exploratory nature of this study. While findings in physical examination and medical history can aid in a differential diagnosis, testing patients for susceptible HLA-types or antibodies related to mesh has unknown predictive values. Currently, only subjective patient or observer described diagnostic modalities are considered in the ASIA criteria, leading to a lack of specificity in discerning patients with ASIA from other syndromes (Table 1) [17]. The current pilot therefore intentionally opposes earlier case series on ASIA by only including patients with at least three major ASIA criteria, to form a narrower but more specific patient population. Consequently, to assess the value of MAT, patients who suffer from light ASIA symptoms or who only slightly match the diagnosis, will be excluded to create a homogeneous population of patients who fit the criteria of ASIA most optimally, to test value of MAT [32]. In addition, patients will be referred to an immunologist to test for identifiable autoimmune diseases and relevant confounders, and to exclude other illnesses that could correctly explain the presented symptoms.

In our pilot, the explanted meshes will all be sent for histopathologic examination to identify ongoing microscopic inflammatory processes and to relate these to potentially positive MAT results, despite earlier research by Fadaee et al. (2019) showing minor to no benefits of this test as proof of any relation between PP and ASIA [33]. Additionally, while presence of (chronic) inflammation, foreign body reaction, and fibrosis surrounding the mesh explant are to be expected, reports of pathology findings can lead to a deeper understanding of the difference between autoimmunity and (normal) foreign body reactions in patients suffering from ASIA [33]. Objective diagnostic modalities for ASIA are essential, and a rapid, low-cost, non-invasive diagnostic test such as MAT could be a vast improvement in the diagnosis of patients; if results are promising and consistent [32].

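### The aim is the additional value of MAT, but the comparator is not named and no described analysis sets MAT against the blood results taken from the same patients at T0

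*Protocol article*

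**What the plan says.** The aim, in the Introduction, is: "Additional value of Mesh Allergy Testing (MAT) shall be assessed as a measure to objectify these complaints". The sentence before it describes testing immunologic and allergic responses. What MAT is meant to add to is not stated.

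Outcomes makes the value of MAT primary: "Primary outcome is the value of MAT as an objective diagnostic test for patients who fit the current ASIA criteria". The value of the immunologic blood tests is listed separately, as secondary.

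Statistical Methods fixes the primary output: "Primary outcome (rate of positive diagnostic tests) will be presented as descriptive statistics (percentage of positive tests) at all predefined time points". The only association analysis described is: "The association between the number of subjective complaints and the presence of objective findings is subsequently calculated via Chi-Square Test", or Fisher's exact test when expected counts are low. Objective findings, named as MAT and blood test, are reduced to yes or no. The text does not say whether they enter as two variables or as one composite.

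Interventions has MAT and blood tests done at T0. Five autoantibody tests (ANA, anti-dsDNA, ANCA, Rf, anti-CCP) belong to the panel drawn from all subjects.

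The Discussion says of the ASIA criteria: "Currently, only subjective patient or observer described diagnostic modalities are considered in the ASIA criteria". Table 1, under Participants, lists as a minor criterion: "The appearance of autoantibodies or antibodies directed at the suspected adjuvant". It also lists specific HLA types (minor) and a typical biopsy (major).

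**The concern.** Additional value is a relative notion and needs a comparator. One natural candidate is the immunologic blood panel, because every patient has it at the same visit and because autoantibodies already form part of the criteria in Table 1. A MAT that marks the same patients as the autoantibodies and a MAT that marks entirely different patients are different findings. Yet both can produce the same pair of positivity percentages.

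The Discussion sentence matters for a related reason. If the criteria held no objective element, a bare MAT positivity rate might be read as objective information gained. Table 1 shows that the criteria do hold such elements, so the rate cannot be read that way without looking at the overlap. The Discussion intends MAT to help with decisions that include high-risk mesh removal, so readers may put weight on how the result is framed.

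**Working it through.** The plan states no figure to reproduce: it gives no expected positivity rates and says that a sample size calculation does not apply. The check has three steps.

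**1. Aim, outcome and analysis side by side.**

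| Element | Where | Content |
|---|---|---|
| Aim | Introduction | additional value of MAT, comparator not named |
| Primary outcome | Outcomes | value of MAT as an objective test |
| Secondary outcome | Outcomes | value of blood tests, listed on its own |
| Primary output | Statistical Methods | percentage of positive tests |
| Association | Statistical Methods | complaint count against yes/no objective findings |

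No row sets MAT against blood results.

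**2. What two percentages leave open.** Let N = 50 (Participants), m = number MAT-positive and b = number blood-positive. I assume that blood positivity is also reported as a percentage. The number positive on both lies between max(0, m + b − N) and min(m, b). The number positive on MAT only therefore lies between m − min(m, b) and m − max(0, m + b − N). The values of m and b are assumptions.

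| m | b | MAT only, smallest | MAT only, largest |
|---|---|---|---|
| 15 | 15 | 15 − 15 = 0 | 15 − max(0, −20) = 15 |
| 10 | 20 | 10 − 10 = 0 | 10 − max(0, −20) = 10 |
| 25 | 25 | 25 − 25 = 0 | 25 − max(0, 0) = 25 |

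Exact (Clopper-Pearson) 95% intervals with N = 50:
- 0 patients: 0% (0 to 7.1%)
- 10 patients: 20% (10.0 to 33.7%)
- 15 patients: 30% (17.9 to 44.6%)
- 25 patients: 50% (35.5 to 64.5%)

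For 15 and 15, independence would give 0.30 × 0.70 = 0.21, or 0.21 × 50 = 10.5 patients. When m + b is at most 50, the width of the range equals the smaller of m and b. The uncertainty therefore shrinks if few patients are positive on either test.

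**3. Whether the complaint association fills the gap.** This depends on the coding that is left open.
- *One composite, positive if either test is positive.* With 15 and 15, full overlap gives 15 + 15 − 15 = 15 positive (30%), and no overlap gives 15 + 15 = 30 (60%). The composite total together with the two percentages would then reveal the overlap, provided that the blood component is defined in the same way throughout.
- *Two separate variables.* Full overlap forces identical complaint tables for MAT and blood. Tables that differ rule out full overlap, but they do not give the MAT-only count.

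A direct cross-tabulation gives the count under either coding.

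**The case against.** The strongest reply is that the comparator is supplied by the reader. The aim ties additional value to objectifying complaints. The Abstract and the Discussion call MAT a first objective screening test or tool, so *additional* may mean beyond subjective complaints. The complaint association partly serves that reading. Autoantibodies are also an imperfect yardstick: they are a minor criterion while eligibility rests on major ones, known autoimmune disorders are excluded, the blood panel serves partly to rule out other disease, and MAT addresses a type IV reaction. Finally, an article may leave a descriptive table to a fuller protocol or analysis plan.

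Much of this stands. The document does not commit the study to yield beyond autoantibodies. What remains is that the comparator is undefined and that the outputs the article does fix leave the MAT-blood overlap to be inferred at best.

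Three stronger readings are tempting, and the documents do not support them.
- A reader might infer that what MAT adds *cannot* be reported. It can: the T0 data are paired, and only the analysis is not described.
- A reader might infer that full overlap and no overlap yield the same planned output. Only the two percentages are the same; step 3 shows that the complaint association may differ.
- A reader might infer that the Discussion sentence itself prevents the assessment. It is background text that drives no eligibility rule, outcome or analysis. The sentence before it acknowledges HLA and antibody testing and calls its predictive value unknown. An unknown predictive value does not make a laboratory test subjective, so the contradiction with Table 1 stands, as a separate matter.

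**Conclusion.** The concern holds in a limited form. The aim names an additional value without a comparator, and no described analysis compares MAT with the blood results from the same patients. At an assumed 15 of 50 positive on each test, the two percentages are compatible with 0 to 15 MAT-only patients (0% to 30%). The size rests on assumed rates; that the two percentages alone do not fix the overlap does not rest on them, unless no patient, or every patient, is positive on one of the tests.

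The article describes no reference standard and no control group without ASIA. MAT-only positives could therefore be false positives, and even a full cross-tabulation would show overlap rather than diagnostic yield or accuracy.

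The conflict between the Discussion and Table 1 is a wording error to be corrected in its own right.

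**What to change.** - **Introduction and Outcomes:** state what MAT's value is additional to (subjective complaints, the autoantibody panel, or both).
- **Statistical Methods:** code MAT and blood results as separate variables. Cross-tabulate T0 MAT against T0 autoantibody status, positive meaning any of ANA, anti-dsDNA, ANCA, Rf or anti-CCP, since these are drawn from all patients. Report MAT-only positivity with an exact 95% CI, labelled as a descriptive measure of overlap.
- **Discussion:** reconcile the sentence on subjective modalities with Table 1, and do not present MAT as the only objective element.

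The cost is one 2×2 table and a few sentences, with no new data or visits. Study Registration gives the current stage as enrolment, so the table can still be specified before analysis.

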### Study Registration

This study is registered under NCT06363903 (clinicaltrials.gov). Current stage: Enrolment.

## Methods

### Study Design

In this multicentre pilot cohort study, five departments in three Dutch centres will be participating: department of General Surgery and department of Allergology, Máxima Medical Centre (Máxima MC, Veldhoven), department of Gynaecology, Amsterdam University Medical Centre and department of Urology and department of Immunology, Maastricht University Medical Centre (MUMC+; Maastricht). Each department will have an outpatient clinic for potential ASIA patients after PP implantation. Patient follow-up will be 1 year. Patients expressing a persisting wish for mesh removal may undergo complete mesh removal if deemed safe by the surgeon. If intra-operative findings lead to limitations in complete removal, mesh will be partially removed. Patients not undergoing mesh removal will be assessed for spontaneous relief of symptoms. These patients can be used as naturalistic comparison against the group of patients that eventually undergo mesh explantation.

